#### Procedures for missing data

Losses to follow-up will be first and foremost analysed in reference to differential selection. As a primary approach, all available participants will be analysed. As a second step, we will perform sensitivity analyses using ‘worst case scenario’ (loss to follow-up equalised to no change or change to a higher AUDIT category) as well as last observation carried forward (LOCF) in the long-term follow-up. As a third step we will analyse whether missing outcome information can represent cases of at least missing at random (MAR). In this latter case multiple imputation of missing variables data will be conducted, and the results compared with those of the available cases analysis.

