#### Data security, quality and management

The same rules for data protection and confidentiality are applied for the computerised client record used in the trial as for clinical records in health care. The password-protected record is kept at the SAH, and is used in the everyday management. De-identified information from each participant’s SAH record (baseline AUDIT, duration and number of calls) and data from interviews will be merged into one database, available to investigators in the study team. All employees at the SAH, as well as the personnel in the study team who access personal information, sign a confidentiality agreement upon employment.

Steps involving data management, analysis and interpretation will be carried out by a study team independent both from the funders and from the SAH management. The study team consist of a project leader, a coordinator, a statistician and the interviewers collecting the data. Withdrawal from participation in the trial will instantly be documented in the SAH record and enable participants to contact the SAH for regular counselling. The study process and recruitment process will be discussed in monthly meetings including personnel from the study team and SAH.

Because of the size and nature of the trial, no interim analyses of the intervention’s effects are planned; moreover we do not expect adverse outcomes or significant results before the endpoint. However, loss to follow-up in the two trial conditions is closely monitored as an indication of unfavourable outcome in any group. For the above reasons, no formal data monitoring committee has been assigned.

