### Statistical methods

The primary analysis will follow a superiority design applying an intention-to-treat (ITT) approach, i.e., analysing participants based on their random allocation. The alternative hypothesis is that the brief, structured intervention is more effective than usual care in promoting change in a client’s alcohol drinking habits.

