#### Statistical analysis

The primary outcome ‘change in AUDIT risk level’ will be analysed as a dichotomous variable where any downward shift (yes/no) from a higher- to a lower-risk level between baseline and follow-up is considered as a clinically meaningful change in drinking habits. The ratio of the cumulative rates of change in the trial groups will constitute the effect measure of the brief, structured intervention versus usual care. General linear models (GLM) will be used to calculate the RR for the outcome event.

Baseline characteristics will be compared between groups in order to detect potential imbalance in predictors of the outcome. If the two groups are not well balanced according to these predictors, multivariable analysis applying logistic regression models will be carried out to estimate odds ratios for the outcome event.

Secondary outcomes (i.e., depression, anxiety, health measures, care seeking) will be analysed using GLM or logistic regression models as described above.

Complementary ‘per-protocol’ and ‘as-treated’ analyses will also be conducted [30]. The ‘per-protocol’ analysis, will only include participants with complete adherence. Complete adherence is defined as: having used the material and received the proactive call (brief, structured intervention); receiving all counselling sessions agreed between the counsellor and the client (usual care). In the ‘as-treated’ analysis, the number of sessions and total duration of the counselling will be considered for each participant, independent of group allocation. These analyses will contribute to the assessment of the effect of the intervention when delivered in standard practice. Possible confounding effects must be carefully monitored in these analyses, since they ignore the random assignment and, therefore, the distribution of baseline risks between participants.

Moderating factors in the analysis include readiness to change, as well as dose-response, i.e., number and length of calls. Further, process data from the records will provide information on the conduct of the proactive calls (adherence).

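### The worst-case analysis counts lost clients as no shift in both arms, which is the worst case for each arm's rate but not for the superiority risk ratio

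*Protocol article*

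**What the plan says.** The missing-data section of the protocol article (Procedures for missing data) sets out a sequence. Losses are first examined for differential selection. Then "As a primary approach, all available participants will be analysed". Next come two sensitivity analyses: a worst-case scenario, defined in parentheses as "loss to follow-up equalised to no change or change to a higher AUDIT category", and "last observation carried forward (LOCF) in the long-term follow-up". Last, the authors judge whether data are missing at random (MAR), and "In this latter case multiple imputation of missing variables data will be conducted".

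The Statistical analysis section defines the event as "any downward shift (yes/no) from a higher- to a lower-risk level between baseline and follow-up" and says "The ratio of the cumulative rates of change in the trial groups will constitute the effect measure". The hypothesis under Statistical methods is that "the brief, structured intervention is more effective than usual care", so evidence for the intervention is an RR above 1. Under Data security, quality and management, "loss to follow-up in the two trial conditions is closely monitored as an indication of unfavourable outcome in any group".

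**The concern.** A worst-case analysis in a superiority trial is normally read as the missing-data assumption hardest on the claim being tested. The rule here is stated without reference to arm. For a yes/no outcome, an unchanged category and a higher category are the same result, a non-event. Giving that result to every lost client in both arms lowers both success rates, and the ratio between them then depends only on which arm lost more.

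The stake is the robustness statement. The Discussion expects attrition that can be large in this population, and says superiority would strongly support moving to the less labour-intensive service. A report that the result survived the worst case would carry more weight than this rule can give it.

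**Working it through.** **Inputs.** Sample size: 30% shift in usual care, 50% in the intervention arm, 300 recruited, at least 250 analysed (125 per arm), 5% level. Abstract: 150 randomised per arm. Planned loss is therefore 25 of 150 per arm. Two-sided testing is assumed, because sidedness is not stated. Counts below are expected counts, so some are fractional. Intervals are Wald 95% CIs on the log RR, with SE = √(1/x₁ − 1/n₁ + 1/x₀ − 1/n₀).

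**The plan's own figure.** Power for 50% vs 30% with 125 per arm, pooled-variance normal approximation:
- z = (0.20 − 1.96·√(2·0.4·0.6/125)) / √((0.25 + 0.21)/125) = (0.20 − 0.1215)/0.0607 ≈ 1.29
- Power = 90.2%, which agrees with the stated value of more than 90%.

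**The rule as a formula.** Let p₁ and p₀ be the shift rates among clients followed up, and d₁ and d₀ the proportions lost (1 = intervention, 0 = usual care). With every lost client set to no shift:

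RR_sens = p₁(1 − d₁) / [p₀(1 − d₀)] = RR_available × (1 − d₁)/(1 − d₀)

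**Equal loss, 25 per arm.**
- Available cases: 62.5/125 vs 37.5/125, RR 1.67 (1.21–2.30), risk difference 20 points.
- Protocol's worst case: 62.5/150 vs 37.5/150 = 41.7% vs 25.0%, RR 1.67 (1.19–2.33), risk difference 16.7 points.

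The RR point estimate is unchanged and the interval is slightly wider. That can still tip a borderline result: 56/125 vs 40/125 gives RR 1.40, p = 0.040, while 56/150 vs 40/150 gives RR 1.40, p = 0.050 (lower limit 0.9997).

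**Unequal loss.** The protocol gives only the total of 50, so these splits are assumptions, shown in both directions.

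| Rates among those followed up | Available-case RR | 15 lost intervention / 35 usual care | 35 / 15 |
|---|---|---|---|
| 50% vs 30% | 1.67 | 67.5/34.5 = 1.96 (1.39–2.76) | 57.5/40.5 = 1.42 (1.02–1.98) |
| 30% vs 30% | 1.00 | 40.5/34.5 = 1.17 (0.79–1.74) | 34.5/40.5 = 0.85 (0.57–1.26) |

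With 39% vs 30% and the 15/35 split, an available-case RR of 1.30 (0.92–1.84) becomes 52.65/34.5 = 1.53 (1.06–2.20) under the rule.

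**Scenarios set against the intervention, 25 lost per arm.** Lost intervention clients are set to no shift throughout.
- Lost usual-care clients shift at the 30% planning rate: 62.5/150 vs (37.5 + 7.5)/150 = 45/150, RR 1.39 (1.02–1.89).
- Lost usual-care clients all shift: 62.5/150 vs (37.5 + 25)/150, RR 1.00 (0.77–1.31).

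**The other planned analyses.** LOCF applies to the long-term follow-up. A client with no follow-up interview has only the baseline value to carry forward, which is again no shift. Multiple imputation runs only if MAR is judged tenable. Neither sets missing outcomes against the intervention.

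**The case against.** Missing = non-response is a common convention, and the protocol spells out its rule, so no reader is misled about what will be computed. Its remark that loss may signal a poor outcome in either group supports coding lost clients as no shift in both arms. The rule is one of several checks. Differential selection is examined first, and loss is monitored by arm, so unequal retention would be noticed. A tipping-point grid is also detail that an article may leave to the analysis plan.

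Much of this stands. The convention is reasonable and should be kept, and the rule is not the plan's only or main check. It does not answer the narrower point: the label promises a worst case, and for the contrast under test the stated rule is not one. That is a fault in what is written, not a missing detail.

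Three stronger readings are tempting but unsupported:
- That the rule can never challenge a positive result under equal loss. The wider interval can tip a borderline one.
- That it can create a positive trial. The primary analysis uses available cases, whose RR stays at 1.00 in the no-effect example above. Only a sensitivity estimate is distorted.
- That the bound of 1.00 shows the planned effect to be fragile. It requires that no lost intervention client and every lost usual-care client shifts, which is an extreme. Under the moderate adverse scenario the lower limit remains just above 1.

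Nor does the protocol indicate which arm will lose more.

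**Conclusion.** The concern holds in this limited form. The rule gives the lowest success rate in each arm, not the least favourable RR for the intervention. Under equal loss it is a weak check on the RR. Under unequal loss its direction depends on which arm loses more, so it may be anti-conservative or conservative. No other planned analysis supplies a scenario set against the intervention. The primary result is untouched; what is unreliable is a claim that the result withstood the worst case.

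The algebra needs only the binary outcome and a rule common to both arms, which is how the text reads. The sizes rest on the protocol's planning rates and total loss, on two-sided Wald intervals, and, for unequal loss, on the assumed splits.

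**What to change.** 1. Rename the present rule 'missing = no shift' and keep it.
2. Add a tipping-point analysis that varies the shift probability among lost clients from 0 to 1, separately by arm.
3. Within it, report a moderate scenario (lost intervention clients do not shift, lost usual-care clients shift at the observed usual-care rate) and the least favourable bound (lost intervention clients do not shift, lost usual-care clients all shift), the latter labelled as an extreme. State where the conclusion changes.
4. Report retention by arm beside each sensitivity RR, so that the retention factor is visible.

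This takes a few lines of code and no new data. The downside is that the robustness statement may be less favourable. Recruitment is described as ongoing and no interim analysis is planned, so the change can be fixed before outcomes are compared.

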##### Usual care

Usual care provided at the SAH is based on MI, with components of CBT [23, 24]. The counselling aims to: develop resistance skills, promote the clients’ motivation to change and prevent recidivism into the use of hazardous amounts of alcohol. Sessions are tailored to the specific needs of each client such as the severity of their alcohol problems and their readiness to change. In practice, the number and duration of counselling sessions vary and the contact mode can be reactive (client-activated) and/or proactive (counsellor-activated). Clients may request contact with the same counsellor in subsequent calls. Since usual care admits multiple counselling sessions, each building on the outcome of the previous one, all client contacts are registered in a computerised client record. Adherence to the agreed contacts is monitored using information from client records. Since usual care is client-activated, there is no standardised protocol for the counselling.

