### Outcomes

#### Primary outcome

The primary outcome will be measured at the 6- and 12-month follow-up, through the alcohol screening instrument, AUDIT, validated to identify problematic alcohol use at the lower end of the spectrum, i.e., hazardous and harmful use [26, 27]. AUDIT encompasses three domains: the use of hazardous amounts of alcohol, dependence symptoms and harmful alcohol use. It consists of 10 questions each scored from 0 to 4, thus yielding a maximum scale score of 40. The scale score can be divided into risk levels: ‘Low risk’ (score 0–7 for men and 0–5 for women), ‘Hazardous alcohol use’ (8–15 for men and 6–13 for women), ‘Harmful alcohol use’(16–19 for men and 14–17 for women) and ‘Highly problematic alcohol use’ (≥20 for men and ≥ 18 women) [22].

The primary outcome in this study is defined as a downward shift in AUDIT risk level (yes/no) between baseline and follow-up. The proportion of participants undergoing this shift will be used to aggregate the data.

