### Sample size

The sample size estimation is based on the primary outcome, i.e., decrease in AUDIT risk category, in a superiority design. Based on a previous observational study of the SAH [12], we estimate that 30% in the usual care group will make a downward shift in AUDIT risk level. We estimate that 300 participants will be recruited to the study, of which at least 250 participants will be included in the analytical sample (125 in each experimental group). Based on the analytical sample the study will have more than 90% statistical power to detect a Risk Ratio (RR) equal to or greater than 1.7 for the alternative counselling (i.e., 50% cumulative rate of change in the brief, structured intervention group) as statistically significant at the 5% level. For a RR of 1.3 the power will decrease to about 50%.

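### The 12-month LOCF sensitivity analysis assumes that no lost 6-month responder relapses, and the effect measure should be worded as a proportion at each visit (minor)

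*Protocol article*

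**What the plan says.** **Outcome.** Under Primary outcome: "The primary outcome in this study is defined as a downward shift in AUDIT risk level (yes/no) between baseline and follow-up". The same section says "The primary outcome will be measured at the 6- and 12-month follow-up". Dissemination of results adds that the two follow-ups will be reported separately.

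**Effect measure.** Under Statistical analysis: "The ratio of the cumulative rates of change in the trial groups will constitute the effect measure". The word *cumulative* is not defined. Sample size uses it again for the planning value, "50% cumulative rate of change in the brief, structured intervention group", set against 30% in usual care.

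**Missing data.** Procedures for missing data begins: "As a primary approach, all available participants will be analysed". The second step is a pair of sensitivity analyses: a worst-case analysis that counts the lost as not improved, "as well as last observation carried forward (LOCF) in the long-term follow-up". The third step is multiple imputation, carried out only if the missing outcomes are judged to be at least MAR.

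**Loss and relapse.** Data security, quality and management says that "loss to follow-up in the two trial conditions is closely monitored as an indication of unfavourable outcome in any group". Usual care lists among its aims to "prevent recidivism into the use of hazardous amounts of alcohol".

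**The concern.** LOCF at 12 months carries the 6-month AUDIT category forward. A client who had shifted down at 6 months and was not reached at 12 months becomes a 12-month success. For these clients the method allows no relapse, in a condition where the protocol itself names relapse as something counselling should prevent and watches loss as a possible bad sign.

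The error need not be equal in the two arms. In the brief arm, counsellors make one proactive call two weeks after the booklet is sent and start no contact after it, though clients may call back. Usual care continues as needed (Fig. 2 caption). Durability between 6 and 12 months is therefore a place where the arms could plausibly differ, and LOCF cannot see such a difference among those lost.

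The wording of the effect measure is a smaller, related matter. For a reversible outcome measured twice, *cumulative* leaves it open whether 12-month success means status at that visit or a shift at either visit.

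**Working it through.** **1. The plan's own figure.** Sample size gives 125 analysed per arm, 30% v 50%, 5% level (two-sided assumed) and power above 90%. With a pooled variance under the null:

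- mean proportion 0.40; null SE = √(2 × 0.40 × 0.60 / 125) = 0.0620
- alternative SE = √((0.30 × 0.70 + 0.50 × 0.50) / 125) = 0.0607
- z = (0.20 − 1.96 × 0.0620) / 0.0607 ≈ 1.29, power 90.2%

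The stated power reproduces when the cumulative rate is treated as one simple proportion per arm.

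**2. What LOCF does to the 12-month comparison.** Let p6 and p12 be the true proportions shifted at each visit, and m the share seen at 6 months but missing at 12. If loss is independent of outcome, the expected LOCF rate is

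(1 − m) × p12 + m × p6.

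Inputs:

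- 150 per arm (Abstract).
- m = 50/300 = 16.7%, the largest loss implied by Sample size, placed wholly between the visits (assumption).
- p12 = 30% in both arms, so the true risk ratio is 1.00 (assumption).
- p6 = 50% brief v 30% usual care. These are the planning proportions, which the protocol does not tie to a visit, so their use here is an assumption.

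Results:

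- Brief: 0.833 × 0.30 + 0.167 × 0.50 = 33.3%
- Usual care: 0.833 × 0.30 + 0.167 × 0.30 = 30.0%
- LOCF risk ratio = 0.333 / 0.300 = 1.11
- Available cases: 30% v 30%, risk ratio 1.00
- Worst case: 0.833 × 0.30 = 25% in each arm, risk ratio 1.00

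**3. Range.** The documents give no relapse or between-visit loss rates. With p12 kept at 30% in both arms:

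| Lost between visits | LOCF RR, 6-month 50% v 30% | Chance of a significant result for brief | LOCF RR, 6-month 40% v 30% |
|---|---|---|---|
| 16.7% | 1.11 | about 9% | 1.06 |
| 25% | 1.17 | about 15% | 1.08 |
| 40% | 1.27 | about 31% | 1.13 |

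The third column belongs to the 50% v 30% scenario (150 per arm, normal approximation). The nominal chance in that direction is 2.5%.

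**4. When part of the loss comes before 6 months.** Those clients carry their baseline level forward and count as not shifted. If half of the 25 lost per arm go before 6 months (assumption), the rates are (125 × 0.30 + 12.5 × 0.50) / 150 = 29.2% and (125 × 0.30 + 12.5 × 0.30) / 150 = 27.5%, a risk ratio of 1.06.

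**5. When durability is equal.** Take 6-month rates of 50% v 40%, 20% relapse in each arm and no new shifts. True 12-month rates are 40% v 32%, risk ratio 1.25. LOCF gives 0.833 × 0.40 + 0.167 × 0.50 = 41.7% and 0.833 × 0.32 + 0.167 × 0.40 = 33.3%, again 1.25. Both rates are too high, but the ratio is unbiased.

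**The case against.** The strongest reply is that LOCF is not the plan's 12-month result. The primary approach is available cases. LOCF comes at the second step, in the same sentence as a worst-case analysis that takes the view of loss expressed under Data security, quality and management. Imputation may follow. Contrasting assumptions are what sensitivity analyses are for. All of this stands, and it is why the point is minor.

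A reader might infer more: that a 6-month shift counts as a lasting success throughout, because *cumulative rates* could mean shifted at either visit. The effect on the result could then be large. Suppose 50% v 40% shift at 6 months, 40% v 15% of these relapse, and no one newly shifts. Status at 12 months is 30% v 34%, risk ratio 0.88, whereas shifted-at-either-visit gives 0.50/0.40 = 1.25. The documents do not support this reading. The outcome is a comparison of baseline with follow-up, the two visits are reported separately, Sample size uses the term for a plain proportion, and no section says that a 6-month shift counts at 12 months. On the same inputs, LOCF with 25 of 150 lost per arm gives 33.3% v 35.0%, risk ratio 0.95. That is closer to 1 than 0.88, but not reversed.

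It is also fair to say that imputation predictors are commonly left to the analysis plan, so their absence is no fault. What remains is the choice of LOCF itself. If MAR is judged implausible, imputation is not run, and LOCF is then the only stated 12-month analysis that uses the 6-month AUDIT of those lost.

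**Conclusion.** The point holds as a minor one. LOCF is a poor sensitivity analysis for this outcome: it assumes no relapse among lost 6-month responders, sits badly with the protocol's own reading of loss, and can favour an arm with a larger but less durable early effect. At the planned loss the distortion is at most about 1.00 to 1.11 under the assumed 50% v 30% at 6 months, less if some loss comes before 6 months, and nil when durability and loss are equal in the arms. It would grow if loss exceeded the plan. The Discussion expects that attrition can be large in this target group.

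The figures rest on assumed 6- and 12-month rates and on loss independent of outcome. Under that independence the available-case and worst-case risk ratios stay at the true value. The plan does not hide relapse in anyone interviewed at 12 months, and its primary comparison is not called into question here. The word *cumulative* is loose rather than wrong.

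**What to change.** 1. Under Procedures for missing data, delete LOCF and keep the worst-case analysis.
2. Run multiple imputation of the missing 12-month AUDIT as a planned sensitivity analysis, with arm, baseline AUDIT and 6-month AUDIT among the predictors. Do not make it depend on first showing MAR, which the observed data cannot establish. This uses the 6-month information without assuming that it persists.
3. Under Statistical analysis and Sample size, replace the cumulative rate of change with the proportion of participants whose AUDIT risk level at that visit is lower than at baseline. This agrees with Primary outcome and Dissemination of results.

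An optional addition is a table, by arm, of 6-month responders who have moved back up by 12 months.

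The cost is a few sentences and slightly more analysis work, with no new data. Success rates in the 12-month sensitivity analyses may look lower than under LOCF.

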## Discussion

Telephone helplines constitute a promising approach to the delivery of brief interventions to consumers of hazardous amounts of alcohol, but high-quality studies are needed to determine their effectiveness. Thus, this study is set up as a randomised control trial evaluating the long-term effectiveness of telephone counselling for the use of hazardous amounts of alcohol intended to reach the general population.

The present evaluation will add to previous knowledge [11, 12] by evaluating two separate counselling models delivered at the SAH. The study results will be, first and foremost, used locally in order to further develop the service provided at the SAH. To this end the results will be disseminated promptly to the stakeholders involved in running the helpline. Further, the study will expand the evidence base for counselling models in telephone services on alcohol prevention and treatment, knowledge suitable for use in broader environments.

The principal advantages of the proposed study are the random allocation of study participants, which minimises bias, and the timing of disclosure which does not interfere with data collection at baseline or willingness to participate. Data collection, conducted with personal interviews, will maximise participation and prevent attrition which can be assumed to be large in the target group. Additionally, assessment of the baseline characteristics and of the outcome measures is blinded to allocation and independent from the SAH setting. Incidentally, the data collection and recruitment procedures are quite robust to critical accidents and deviations as they were piloted before the initiation of the trial. In order to monitor the process, data on programme fidelity and participants’ compliance to the intervention will be collected. This information will enable secondary approaches, such as per-protocol and as-treated analyses.

The study also has some limitations. Because of ethical concerns, it was not possible to have a ‘non-treatment’ control group in the SAH setting. The downside of this is the limitation in drawing inference about the effect of the usual care delivered at the SAH.

However, the pragmatic design provides results on the effectiveness and, thus, implications for practical usability of the results. If the brief, structured intervention proves superior to usual care, this would be a strong indication to change to a less labour-intensive method.

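### Multiple imputation is made conditional on a finding of missing at random that observed data cannot supply, and the analyses left without it cannot show arm-specific informative loss when loss is equal by arm

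*Protocol article*

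**What the plan says.** The section on procedures for missing data opens with a look at whether losses are selective and then sets out three steps.

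- Primary: "As a primary approach, all available participants will be analysed".
- Second step, with no condition attached: "As a second step, we will perform sensitivity analyses using ‘worst case scenario’ (loss to follow-up equalised to no change or change to a higher"; the scale meant is the AUDIT risk level. Last observation carried forward (LOCF) is added for the long-term follow-up.
- Third step: "As a third step we will analyse whether missing outcome information can represent cases of at least missing at random (MAR". The condition follows: "In this latter case multiple imputation of missing variables data will be conducted, and the results compared with those of the available cases analysis".

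The Sample size section gives the expected numbers: "300 participants will be recruited to the study, of which at least 250 participants will be included in the analytical sample (125 in each experimental". The section on data security, quality and management says that loss by arm is "closely monitored as an indication of unfavourable outcome in any group". The Discussion says that personal interviews will "prevent attrition which can be assumed to be large in the target group".

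**The concern.** MAR and MNAR differ in how loss relates to AUDIT values that were never observed. Comparing completers with non-completers on baseline data can give evidence against missing completely at random, but no such comparison can establish MAR. The decision to impute therefore rests on a judgement that the data cannot support, and it would be taken after the pattern of loss is known.

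If the judgement goes against MAR, the trial reports the available-case result without the imputation comparison. Yet the available-case risk ratio generally needs the stronger assumption: within each arm, loss must be unrelated to outcome. Imputation needs this only after conditioning on the predictors in the model. Doubt about MAR is thus no reason to prefer available cases.

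At stake is whether the reported sensitivity analyses could show a reader that the primary result depends on who was lost.

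**Working it through.** **The plan's own figures.** Expected loss is (300 − 250)/300 = 16.7%, and 250/(1 − 1/6) = 300. For 125 per arm and 30% v 50%, two-sided 5%, pooled variance under the null: z = (0.20 − 1.96 × √(2 × 0.40 × 0.60/125)) / √((0.21 + 0.25)/125) = (0.20 − 0.1215)/0.0607 = 1.29, so power is 90.2%. This agrees with the stated figure of more than 90%, and nothing below changes it.

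**Why the worst case can leave the risk ratio (RR) unchanged.** The outcome is yes/no, so no change and a move to a higher category are both coded as no. Let p be the true rate in an arm, m the fraction lost and q the rate among the lost.

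- Available-case rate = (p − m·q)/(1 − m)
- Worst-case rate = p − m·q = (1 − m) × available-case rate
- Hence worst-case RR = available-case RR × (1 − m₁)/(1 − m₀), where 1 is intervention and 0 is usual care

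The multiplier depends only on retention, not on how the lost clients fared. With m₁ = m₀ it is 1.

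**Illustration 1, equal loss.** From the protocol: p = 30% in usual care ("we estimate that 30% in the usual care group will make a downward shift in AUDIT risk level") and m = 16.7% overall. Assumed: p = 30% in the intervention arm too (true RR 1.00), the same m in each arm, q₁ = 10%, q₀ = 30%.

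- Available cases: (0.30 − 0.1667 × 0.10)/0.8333 = 34%; (0.30 − 0.1667 × 0.30)/0.8333 = 30%; RR 1.13
- Worst case: 0.30 − 0.0167 = 28.3%; 0.30 − 0.05 = 25%; RR 1.13
- MAR imputation by arm without predictors that explain the loss: lost clients take the observed 34% and 30%; RR 1.13
- Imputation with an arm-specific shift of 10% − 34% = −24 percentage points for lost intervention clients and none for usual care: 0.8333 × 0.34 + 0.1667 × 0.10 = 30%; RR 1.00

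If loss is instead assumed to be 30% per arm, available cases give 0.27/0.70 = 38.6% v 30%, RR 1.29, and the worst case gives 27% v 21%, again RR 1.29.

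If q is 10% in both arms at 16.7% loss, available cases give 34% v 34%, RR 1.00. The bias comes from the assumed difference between arms.

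**Illustration 2, unequal loss.** Assumed throughout: true RR 1.00; a binary baseline predictor, half the clients in each stratum, with 45% and 15% shifting; usual-care loss 10%. Intervention loss is about 23%, arising in three ways.

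| Loss in the intervention arm | Available cases | MAR imputation using the predictor | Worst case |
|---|---|---|---|
| Depends on predictor only (MAR): 7% and 40% | 1.11 | 1.00 | 0.94 |
| Depends on predictor and outcome (MNAR): 9% of non-shifters and 3% of shifters in the 45% stratum; 45% and 15% in the other | 1.23 | 1.13 | 1.04 |
| Depends on outcome only (MNAR): 30% of non-shifters, 8% of shifters | 1.20 | 1.18 | 1.02 |

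First row in full: available-case intervention rate = (0.5 × 0.45 × 0.93 + 0.5 × 0.15 × 0.60)/(0.5 × 0.93 + 0.5 × 0.60) = 0.25425/0.765 = 33.2%, against 30%, RR 1.11. Imputation within strata restores (45% + 15%)/2 = 30%, RR 1.00. The worst case gives 0.25425/0.27 = 0.94.

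In these cases imputation is closer to the truth than available cases. It is a full correction only under MAR.

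**The case against.** The strongest reply is that the plan does not leave the primary result untested. The worst case runs unconditionally and is itself an MNAR-type assumption, and selective loss is examined first. This stands as far as it goes. With unequal loss the worst case does move the RR, and in the two MNAR rows above it lands nearer to 1.00 than imputation does. But it moves by a factor set by retention alone: it overshoots to 0.94 in the MAR row and does not move at all when loss is equal. LOCF is planned only for the long-term follow-up, so it adds nothing at 6 months; at 12 months it assumes no change in either direction since the earlier interview.

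A reader might infer more than the documents support in four ways.

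- *That imputation is dropped exactly when the primary result is most doubtful.* A gate that cannot detect MNAR cannot do that reliably; it withholds imputation on an unsupported judgement.
- *That imputation would have corrected the 1.13.* Illustration 1 is MNAR, and MAR imputation without explanatory predictors returns the same value.
- *That the plan admits informative loss that differs by arm.* The monitoring sentence explains why no data monitoring committee was set up, and it applies to any group. The Discussion expects interviews to limit attrition. The difference between arms, and any loss above 16.7%, are assumptions here.
- *That available cases contradict the intention-to-treat label.* The Statistical methods section defines intention-to-treat as analysis by allocated arm, and available cases analysed by arm meet that definition.

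It is also fair to say that imputation models and delta values are commonly left to a statistical analysis plan, which is not at hand. Their absence is not the point. The gate is a rule that the article states.

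**Conclusion.** The point holds in a limited form. The article fixes a decision rule that cannot be operated as written, because no analysis of the observed data can show that loss is MAR rather than MNAR. If MAR is not accepted, what remains is an available-case result that generally needs a stronger assumption, plus a worst case that cannot reveal arm-specific informative loss when loss is equal by arm.

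The possible size, under assumed values only, is an RR of 1.13 in both analyses when the truth is 1.00 and loss is 16.7% per arm, or 1.29 if loss reached 30%. These figures measure what the remaining analyses can miss. They do not measure the harm done by omitting MAR imputation. The weakness lies in the sensitivity analyses; the planned primary estimator, the sample size and the stated power are not shown to be wrong by it. It should be changed, and the change is small.

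**What to change.** 1. Delete the MAR check as a condition for imputation. The comparison of completers with non-completers can stay as description.
2. Run multiple imputation under MAR for all randomised clients as a planned sensitivity analysis, whatever that comparison shows. Impute by arm, using data already collected: sex, baseline AUDIT and M.I.N.I., 6-month AUDIT for the 12-month outcome, and the number and length of contacts in the helpline record, which do not depend on response to the follow-up interview.
3. Add a delta-adjusted analysis over a prespecified range, with the departure from MAR allowed to differ by arm, and report how large a difference would change the conclusion.
4. Keep the worst case and LOCF, if wanted, as secondary checks.

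The cost is slightly more analysis work. No new data are needed, and sample size and stated power do not change.
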